## Recruitment modalities

The recruitment will be done within the ICU departments of the centers participating in the study. It is planned to include 950 patients admitted to the intensive care unit and justifying an orotracheal intubation procedure, after reading the information letter and collecting the consent of the patient or the trusted person, or carrying out the emergency inclusion procedure. In the last two cases, the patient's consent will be collected posteriori after reading the information letter. Patient will be followed until day 28 or death.

# Study design AND CONDUCT

## Study schedule

Consecutive ICU patients requiring ETI will be randomly allocated to ETI with or without ORI monitoring before beginning of preoxygenation, with stratification by centre, expert or nonexpert intubator status (experts: ≥5 years’ ICU experience, or ≥1 year ICU experience plus ≥2 years’ anaesthesiology training) (24), and NIV or others devices for preoxygenation. Two intubators including at least one expert will be present throughout ETI. At least one of the intubators will be trained in ORI monitoring, i.e., will have attended an education session and used the device twice.

Randomisation will be via an electronic case-report form, using a balanced scheme with stratification as described above.

Informed consent will be obtained from the patient or next of kin.

Patients for whom no family member is available to receive information and consent to participate in the study within a time frame compatible with the study design will be included in the study after completion of an emergency consent form by the patient's attending physician. Informed consent will be sought from the patient upon regaining decision-making capacity.

Data collected:

- Patient characteristics: demographics, Simplified Acute Physiologic Score II, activity level (Knaus), Charlson comorbidity index, ICU admission diagnosis, reason for ETI, Sequential Organ Failure Assessment [SOFA] score, vital signs at enrolment, criteria for difficult face-mask ventilation, criteria for difficult intubation, and MACOCHA score
- Before, during ETI, and 2 minutes after successful ETI: ORI, Mallampati score, pre-oxygenation methods and duration, type and dosage of sedatives and neuromuscular blockers, Cormack-Lehane grade, glottic opening score, number of ETI attempts before success (each introduction of the laryngoscope into the mouth is a separate laryngoscopy attempt), with details: manoeuvres during laryngoscopy, reason for ETI failure, difficult ETI , duration of ETI , need for face-mask ventilation after first ETI attempt, need for gum elastic bougie, and types of life-threatening and other complications. Pulse oximetry will be recorded throughout the ETI procedure.
- Day 1 to 7: SOFA score
- Day 28: Mortality, ICU stay length, hospital stay length, cognitive score (F-TICS-m)

**STUDY SCHEDULE**

| **Activities** | D0  (Inclusion visit) | D1 to D28 | D28 |
| --- | --- | --- | --- |
| Participant information | X |  |  |
| Consent | X |  |  |
| Randomization | X |  |  |
| Previous medical history | X |  |  |
| Clinical examination | X | X |  |
| Efficacy and/or safety assessment | X | X |  |
| Para-clinical examinations | X |  |  |
| Compliance | X |  |  |
| Adverse events |  | X | X |
| Phone contacts |  |  | X |

# General study methodology

The study presents the following characteristics:

- Study of preoxygenation during intubation in intensive care,
- Multi-centre national study,
- Controlled, superiority, 2 arms,
- Randomised stratified,
- Open label trial, with unified outcome assessmentParallel group study.

## Study diagram

[figure not shown]

SoC: Standard of Care

## Description and justification of the treatment plan / method under study

### Treatment plan

Monitoring of the SpO2 will be determined at the beginning of the intubation procedure continuously by 2 sensors (local sensor, and Masimo Rad 7) for all patients. All values will be entered into an eCRF. Each sensor will be placed on index, middle and ring fingers of each hand.

Evaluation of difficult intubation and difficult ventilation will be performed in accordance to factors previously validated: This evaluation will be captured in the electronic case report form (body mass index, mouth opening, thyro-mental distance, Mallampati score, snorer, toothless, sleep apnea) according to De Jong *et al* (25).

ETI is performed in both groups according to the protocol outlined below.

(a) Pre-oxygenation is achieved using the device chosen by the doctor in charge of the patient:

- Bag valve mask delivering oxygen at a minimum flow of 60 L/minute for at least 3 minutes (26–28);
- Non-rebreathing (high-concentration) mask delivering oxygen at a minimum flow of 60 L/ minute for at least 3 minutes (28,29);
- Ventilator in NIV mode providing 100% FiO_2_ for at least 3 minutes (12);
- High-flow nasal oxygen device (e.g., Optiflow^®^) delivering oxygen at a minimum flow of 60 L/minute, with 100% FiO_2_, for at least 3 minutes (30,31).

Choice of preoxygenation device will be at physician discretion but Non Invasive Ventilation will be advised in case of oxygen flow > 8l/min to obtain SpO2≥95%. Additionally, apneic ventilation will be also advised (22).

Preoxygenation will be delivered according to protocol defined with each local primary investigators. Cut-off of 0.6 for ORI objective at the end of the preoxygenation was adopted according to re-analysis of previous data (personal data, not published).

[figure not shown]

(b) Anaesthesia is then induced by injecting a hypnotic agent and a neuromuscular blocking agent. The type and dosage of these drugs is at the discretion of the doctor performing the intubation. Nevertheless, in agreement with international (7) and French guidelines (8), the following two principles are applied:

- The preferred neuromuscular blocking agent in the absence of contra-indications (e.g., hyperkalaemia, burn injury more than 24 hours earlier, spinal lesion, or allergy) is succinylcholine in a dosage of 1 mg/kg. The alternative is rocuronium 1 mg/kg, provided the antidote sugammadex (16 mg/kg) is available.
- If possible, the hypnotic agent is either hypnomidate 0.2-0.3 mg/kg or ketamine 1-2 mg/kg.

(c) Laryngoscopy is performed using the device choose by physician in charge. The size of endotracheal tube and the size of the Macintosh laryngoscope were chosen by the physician at bedside.

(d) ETI is then performed. The cuff of the endotracheal tube is inflated and the tube is connected to the ventilator. If this first ETI attempt fails, the doctor chooses between a second laryngoscopy and an alternative ETI technique. Alternative ETI technique will be chosen at physician discretion and in accordance to French guidelines (7). Each introduction of the laryngoscope into the oral cavity of the patient is considered a separate laryngoscopy attempt. Use of Sellick’s manoeuver [pressure applied to the cricoid cartilage] during ETI is at the discretion of the doctor in charge of the patient and is recorded in the electronic case-report form [eCRF]. Intra-tracheal tube position is confirmed by analysing the capnography curve over four or more breathing cycles. Total ETI duration is defined as the time from anaesthesia induction initiation to observation of the first inflection on the expired capnography curve (confirming intra-tracheal tube position). All items of electronic case report form were analysis on real time by a third person not in charge of patient’s care.

During intubation procedure, blinded continuous monitoring of SpO2 and ORI (for control group) will be performed by appropriate monitor (Masimo Rad7) with data extraction at regular intervals. Oxygen saturation will be tracked during ETI by research nurse or assistant nurse dedicated to fill the eCRF. ORI evolution will not be provided to investigators in the standard of care group. In the control group, local continuous monitoring of SpO2 will be performed with local pulse oximeter device.

## Identification of all data sources not included in the medical record

Clinical, laboratory and background data will be collected at the time of enrolment, during the ICU-stay, at ICU-discharge, at hospital-discharge, and at follow-up. Data will be obtained from hospital records, relatives, and will be entered into a web-based electronic case record form (eCRF) by site personnel. The site investigator must sign all eCRFs before trial completion to verify that the recorded data is correct and complete. Data from the web-based forms will be migrated to a trial database, which will be handled by the coordinating team. Data not obtainable will be registered as missing and measures to obtain data should not delay intervention or concomitant treatment (i.e. central line not in place at the time of data collection).

Collected data will include:

- Baseline: Inclusion and non-inclusion criteria; demographics; significant comorbid diseases
- Data on hospital admission: temperature on admission; neurological assessment; cause of arrest and diagnostic work-up (i.e. EKG, echocardiography …); Sequential Organ Failure Assessment (SOFA) score; presence of shock on admission; administered therapies
- In the ICU: characteristics of intubation process (drugs, duration)
- Daily during the ICU stay: SOFA score; adverse events
- Outcome and therapies received at ICU discharge
- Outcome and cognitive function at 28 days after randomization

## Rules for discontinuing subject participation

### Patient withdrawal from the study

The patients or next of kin may ask to withdraw from the study at any time and for any reason. According to French law, in the event of secondary withdrawal of consent to participation in the research project, the data collected from study inclusion to withdrawal of the patient will be used. Data collection will be stopped in compliance with the wishes of the patient or next of kin. Withdrawal of a patient from the study will have no impact on the standard care delivered to the patient for the condition that prompted the hospital admission. All investigations and treatment decisions will be at the discretion of the physician in charge of the patient.

Should a patient be lost to follow-up, all data for that patient collected since study inclusion will be used, and the investigator will make every effort to contact the patient.

If a patient included in the emergency procedure died before the collection of his or her consent to continue and no next-of-kin consent could be collected, then his or her data will not be retained and that patient will be excluded from the analysis.

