# Justification of the study

## Positioning of the study

Endotracheal intubation (ETI) is a common procedure in ICUs (1). The risk factors in ICU patients result in a high complication rate (up to 50%) (2). Severe complications are severe hypoxaemia (25%), severe hypotension (25%), cardiac arrest (1-3%), and death (0.5-3%) (1,3,4). Risk factors for potentially fatal hypoxaemia are hypoxaemia before ETI and/or difficult ETI (5). Hypoxemia during ETI is associated with cardiac arrest occurrence (3,6) and morbidity.

Predicting hypoxaemia during ETI is challenging (5). Pre-oxygenation is universally recommended to reduce the risk by prolonging the safe apnoea time (7,8). Pulse oximetry saturation (SpO_2_) is monitored in ICU but only detects late-stage hypoxaemia. FeO_2_ is not available for assessing pre-oxygenation efficacy in the ICU. And this technique has limitations in the emergency setting (sensitivity to leaks) and is not available in ICUs (9). Moreover, in critically ill patients, particularly those with acute hypoxemic respiratory failure, FeO_2_ may not be a reliable measure of the effectiveness of preoxygenation: the reduction in functional lung volume leads, on the one hand, to a reduction in FRC (Fonctional Residual Capacity) and, on the other hand, to a shunt that reduces the efficiency of the alveolar-capillary interface (10). The result is that both SpO_2_ and FeO_2_ can be high while PaO_2_ is low. PaO_2_ can be considered the reference standard for evaluating the effectiveness of preoxygenation but unfortunately cannot currently be obtained at the bedside in real-time in clinical practice (9). Non-invasive ventilation (NIV) is currently recommended for patients with severe hypoxaemia but is associated with a higher risk of severe hypotension (11–15). Last, extended duration of preoxygenation did not help to increase quality of its own (16). Thus, at present, the effectiveness of pre-oxygenation cannot be evaluated in ICUs. Predicting the risk of hypoxaemia during ETI and optimising pre-oxygenation are two major therapeutic goals. A reliable tool for assessing the quality of pre-oxygenation is therefore needed.

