## Inclusion criteria

- ICU admission and need for ETI to allow mechanical ventilation
- Need for supplemental oxygen (via any device and at any flow rate) to obtain SpO_2_>97%
- Patient or next of kin informed about the study and having consented to participation of the patient in the study (patients with coma are unable to consent). If patient is no competent and no next of kin can be contacted during screening for the study, trial inclusion will be completed as an emergency procedure by the ICU physician, in compliance with French law
- Patients affiliated to a social security system

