### Choice of subjects to be included in analysis

Modified Intention-to-treat (mITT) analyses will be performed. This population will exclude patient with no legal requirement.

Per protocol analyses will also be performed and will exclude patient with failure of ORI capture, failure of ORI recording or ORI<0.6 at the end of the procedure.

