### Emergency consent form collection

If the family member is not present, it will be derogated to the consent collection obligation at the time of inclusion. This request will be appreciated by the Ethics Committee (EC). Patients for whom no relative is available to receive information and consent to study participation within a timeframe compatible with the study design, will be included in the study after a statement from the physician in charge of the patient confirming that the patient is not available to receive the information, that the situation is an emergency and that no family member is present. Informed consent will be sought from the relative as soon as possible and then from the patient as soon as he or she recovers decision-making competency.

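### The consent rule for emergency inclusions removes only patients who died, so mortality is understated whenever the rule is applied

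*Protocol*

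**What the plan says.** Section 4.2 (Inclusion criteria) plans for patients who are not competent and have no reachable relative: "trial inclusion will be completed as an emergency procedure by the ICU physician, in compliance with French law". Under section 9.4 (Emergency consent form collection), consent is then sought afterwards, first from a relative and later from the patient.

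Section 6.4 (Patient withdrawal from the study) sets three data rules:

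- Consent withdrawn later: "the data collected from study inclusion to withdrawal of the patient will be used".
- Lost to follow-up: "all data for that patient collected since study inclusion will be used".
- Death after emergency inclusion, with neither the patient's agreement to continue nor a relative's consent obtained: "then his or her data will not be retained and that patient will be excluded from the analysis".

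The third rule exempts no endpoint. Section 7.2 (Choice of subjects to be included in analysis) defines the modified intention-to-treat set in matching terms: "This population will exclude patient with no legal requirement". It does not define that phrase further.

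Death is part of the safety composite (section 2.2). It is the event in the ICU and 28-day mortality analyses, and the competing event in the length-of-stay analysis (both section 7.2).

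**The concern.** This exclusion is made after randomisation and is triggered by an outcome. A patient can meet the rule only by dying, and no text removes an emergency-included survivor merely because consent is still pending. Numerator and denominator of every mortality estimate therefore lose the same patients, all of them events. Consent is sought after inclusion, so an earlier death leaves less time to obtain it, and deaths close to the procedure are the most exposed.

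The lowest saturation is recorded around intubation, normally before the rule applies, so primary endpoint values already collected are discarded as well. Multiple imputation (section 7.2) cannot help, because these patients are no longer in the analysis set. What is at stake is the accuracy of the reported mortality and death component and, if removals differ by arm, the comparisons themselves.

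**Working it through.** **The plan's own figure.** Inputs from section 7.2: difference 2 points, SD 10, two-sided alpha 0.05, power 85%, 5% cross-over, no missing data. The two-means formula gives 449 per arm, 898 in total; 898/0.95 = 946 after rounding up, which agrees with the stated 950. Power with 475 × 0.95 ≈ 451 per arm is 85.2%. The calculation contains no allowance for patients removed on consent grounds.

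**Inputs the protocol does not give (assumptions).** Mortality m before consent, 20–40%; share e included by the emergency route, 20–60%; share u of those deaths with no kin consent, 10–50%.

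**Formulas.** Fraction removed: x = m·e·u. Observed mortality: (m − x)/(1 − x). If removed patients have a lowest saturation D points below the mean of all randomised patients in their arm, that arm's observed mean rises by D·x/(1 − x).

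**Absolute mortality.** With m = 0.30, e = 0.40, u = 0.30: x = 0.036, and 950 × 0.036 = 34.2 patients. Observed mortality is (0.300 − 0.036)/(1 − 0.036) = 0.264/0.964 = 27.4%. Over the whole range, 3.8 to 114 patients are removed and mortality is understated by 0.3 to 8.2 points.

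**Mortality contrast** (true mortality 30% in both arms, e = 0.40).

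| u in one arm | u in the other | Observed mortality | Spurious difference |
|---|---|---|---|
| 30% | 30% | 27.4% vs 27.4% | 0 |
| 20% | 40% | 28.3% vs 26.5% | 1.8 points |
| 10% | 50% | 29.1% vs 25.5% | 3.6 points |

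Second row: x = 0.024 gives 0.276/0.976 = 28.3%; x = 0.048 gives 0.252/0.952 = 26.5%.

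**Primary contrast.** Same 20% vs 40% case with D = 10: 10 × (0.048/0.952 − 0.024/0.976) = 10 × (0.0504 − 0.0246) = 0.26 points, against the 2-point target. With equal removals of similar patients the shift is zero.

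**Power.** At x = 0.036, power falls from 85.2% to 83.9%; over the whole range it lies between 80.4% and 85.0%.

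**Peri-intubation deaths.** Section 1.1 cites 0.5–3%: 950 × 0.005 = 4.75 and 950 × 0.03 = 28.5. With e·u = 0.40 × 0.30 = 0.12, about 0.6 to 3.4 of these would be removed. A higher u for very early deaths would raise that number.

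**The case against.** The rule needs three things together: emergency inclusion, death before the patient's own consent, and no kin consent. Relatives are approached as soon as possible after an emergency inclusion, dedicated relative forms exist for that situation (Appendices 8 and 8bis), and section 6.4 does not say that kin consent must precede death. A reader might infer that most peri-intubation deaths disappear; the documents give no emergency share or consent rate that would support this. The event rates in section 1.1 also describe ICU intubation in general, whereas this trial excludes patients with too little time to randomise. This objection stands.

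A reader might also infer that an imbalance in removals could never be detected. That goes too far. Randomisation is electronic and issues an inclusion number automatically (section 7.2), deletions are logged in an audit trail (section 7.1), and a data review precedes the database freeze. Counts per arm should be recoverable, although the protocol does not require them to be reported.

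Nor do the three rules in section 6.4 contradict each other. Withdrawal presupposes that consent was given, and the protocol attributes keeping those data to French law. For the patients at issue, neither the patient's consent to continue nor kin consent was ever obtained. The deletion may be a legal obligation; the protocol cites no legal basis for it, and the documents cannot settle the matter. A legal basis would explain the rule but would not remove its effect on the estimates.

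Finally, no mechanism is given by which ORI monitoring would change whether relatives can be reached. This is a fair argument against assuming bias in the contrast. It does not exclude it: the trial is open label, and any difference in early deaths would itself make removals unequal.

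**Conclusion.** The point holds in a limited form. As written, the plan understates ICU and 28-day mortality as soon as one patient meets the rule, and understates the death component of the composite if any of those deaths was peri-procedural. The direction is certain; the size is not. The central illustration (30.0% observed as 27.4%, about 34 patients) rests wholly on assumed rates.

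Bias in the treatment comparisons is conditional on removals that differ in number or type by arm. Under the 20% vs 40% assumption it is about 1.8 points for mortality and 0.26 points for the primary endpoint. A reader might infer that the primary result is seriously threatened. That would need a large excess of removals in one arm with extremely low saturations, and nothing in the protocol makes that likely.

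**What to change.** Amend section 6.4 (Patient withdrawal from the study) and section 7.2 (Choice of subjects to be included in analysis) to:

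1. Require a non-identifying count per arm of patients who were randomised by emergency inclusion, died before consent and had no kin consent, and report it in the flow diagram.
2. Pre-specify a sensitivity analysis of ICU and 28-day mortality that counts these patients as deaths in their randomised arm. With counts alone this compares proportions; a Cox model would need dates of death. For the peri-intubation composite, use best-case and worst-case bounds instead, because some of these deaths may have occurred well after the procedure and should not all be counted as procedural events.
3. Ask the ethics committee whether procedure data and vital status up to death may lawfully be kept when nobody objected, and keep them if so.

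The cost is a protocol amendment through the route in section 9.6, possibly with revised information and consent forms, plus a small amount of extra analysis. It should be settled before any records are discarded. If the committee refuses retention, items 1 and 2 can still be done from allocation counts.

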### Discontinuation of all part of the study

The study will be completed after collection of the day 28 data for the patient included last in the study. Given that this research investigates standard practice and has minimal risks and constraints, the only pre-defined study discontinuation criterion is a scientific publication resulting in a consensus that challenges the primary study hypothesis or the method used to optimize oxygenation during intubation for patient in intensive care.

# Data Management AND STATISTICS

## Data entry and data collection

All the study data are collected routinely in ICUs for the management of comatose mechanically ventilated patients:

- Demographics and clinical data
- Treatments given: daily until hospital discharge
- Laboratory data
- Nosocomial infections
- Invasive devices

### Data entry, processing and circulation

Data collection for each person participating in the research is realized with an electronic case report form (eCRF).

Each person responsible for the filling of the eCRF (investigator, ARC ...):

• will have to be identified in the table of delegations of responsibilities of each center (see investigator’s file).

• Will have a “user” account with specific computer rights linked to his role (right to enter or modify a data, right to lock, monitor or sign a page of eCRF ...)

Entering, viewing or modifying data will only be possible via the eCRF pages (input masks), on <https://nantes-lrsy.hugo-online.fr/CSonline>.

The data will be stored directly from the eCRF into the database hosted on a dedicated server, with controlled access (account/password) according to the user role. Any addition, modification or deletion of data will be recorded in a non-editable electronic file (the audit trail)

